**Trial registration number:**

NCT03441906.

Strengths and limitations of this studyThe international design allows for comparison of healthcare systems and its influence on total interval length.Multicentre, prospective design allows reliable comparison of sarcoma subgroups to make clinically relevant recommendations to improve total interval.Inclusion of patients at diagnosis minimises recall bias for total interval length.Patients were actively involved in the design of this study and mentioned earlier diagnosis and patient-reported outcomes as research priorities.

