## Methods and analysis

### Study design and setting

We will conduct a longitudinal, prospective, cohort study among adult sarcoma patients, newly diagnosed in one of the participating study centres (five centres in the Netherlands: Radboud University Medical Centre Nijmegen, Erasmus Medical Centre Rotterdam, University Medical Centre Leiden, University Medical Centre Groningen, Netherlands Cancer Institute Amsterdam; three centres in the UK: The Royal Marsden London, Christie Manchester, Royal Orthopaedic Hospital Birmingham, all NHS Foundation Trusts). The study started recruitment at the first centre in the Netherlands in February 2018 and in the UK in October 2018 and is currently recruiting.

After informed consent, patients are being asked to complete questionnaires at five points in time: the first at baseline, preferably before start of treatment or within 4 weeks thereafter, and at 3, 6, 12 and 24 months follow-up (table 1). Baseline questionnaire completion will take about 45 min, follow-up questionnaires will take 20–30 min each.

**Table 1 T1:** Time points and questionnaire items

Item (number of items)	Scale	0 months	3 months	6 months	12 months	24 months
Characteristics						
Sociodemographic (max 20)		X	X	X	X	X
Comorbidity (15)	SCQ	X			X	X
Total interval (max 42)	Own design	X	X	X	X	X
Health literacy (1)	SBSQ	X				
Social support (1)	QLCS	X		X		X
Self-efficacy (10)	GSE	X				
Coping (28)	Brief COPE		X			
Resilience (6)	BRS			X		
Outcomes						
Health-related quality of life (30)	EORTC QLQ-C30 version 3.0	X	X	X	X	X
Quality-adjusted life years (6)	EQ5D5L	X	X	X	X	X
Psychological distress (14)	HADS	X	X	X	X	X
Financial impact (20)	Own design	X	X	X	X	X
Information provision (max 26)	Profiles registry		X			
Quality of care (max 23)	PSQ-18 and 3–5 single items	X	X	X	X	X
Total number of items		194	158	105	113	114

BRS, brief resilience scale; COPE, Coping Orientation to Problems Experienced; EORTC QLQ, European Organisation for Research and Treatment of Cancer Quality of Life Questionnaire; EQ5D5L, European Quality of life 5 Dimensions 5 Levels; GSE, general self-efficacy; HADS, hospital anxiety and depression scale; PSQ, patient satisfaction questionnaire; QLCS, quality of life-cancer survivors; SBSQ, set of brief screening questions; SCQ, self-administered comorbidity questionnaire.

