### Participants

Eligible patients are invited by their treating physician or a member of the research team. Inclusion criteria are: (1) aged ≥18 years; (2) new histological diagnosis of sarcoma as confirmed by a sarcoma histopathologist (according to the International Statistical Classification Of Diseases And Related Health Problems, 10th revision, German Modification (ICD-10-GM) codes C40 and C41 for bone sarcoma and C49 for soft-tissue sarcoma); (3) able to communicate in English or Dutch and to complete questionnaires themselves; (4) mental capacity to provide informed consent and participate in the study (as determined by the healthcare professional) and (5) diagnosed at or referred to one of the participating hospitals. Exclusion criteria are: (1) too ill to complete questionnaires (according to treating physician—patients who experience symptoms are still eligible); (2) desmoid fibromatosis and gastrointestinal stromal tumours due to the different nature of the diseases (ICD-10-GM codes C15-20, C26, C48 and C80).

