Change in HRQoL during the follow-up period of 2 years and factors associated with changes in HRQoL will be analysed using repeated measures mixed models. This will be compared between patients with a short and long total interval, using repeated measures analysis of variance, controlling for relevant patient and tumour characteristics, and the patient’s baseline score. Clinically relevant differences will be assessed using Cocks’ method.^41 42^

Other patient-reported outcomes such as QALYs and psychological distress will be analysed in the same way.

Multivariate analyses will be performed to examine associations between total interval length and (1) QALYs, (2) psychological distress, (3) stage at diagnosis and (4) tumour size. These analyses will be corrected for potential confounders including patient and tumour characteristics and healthcare system.

Both unadjusted and adjusted multivariate Cox proportional hazard regression analyses will be used to examine whether a long total interval is associated with PFS or OS.

PFS is defined as the time interval between diagnosis until clinical or radiological progression, as assessed by the treating consultant. OS is defined as the time from diagnosis until death.

Statistical analyses will be performed using IBM SPSS V.25.0; two-sided p values <0.05 will be considered statistically significant.

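### OS is timed from diagnosis but patients join only at a later consent, so the OS data are left-truncated and the Cox models should use delayed entry

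*Protocol article*

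**What the plan says.** Under Statistical analysis the protocol article fixes the time origin and the model. For survival, "OS is defined as the time from diagnosis until death". For progression, "PFS is defined as the time interval between diagnosis until clinical or radiological progression, as assessed by the treating consultant". Unadjusted and adjusted "Cox proportional hazard regression analyses will be used to examine whether a long total interval is associated with PFS or OS".

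The entry rules stand elsewhere. Participants requires a "new histological diagnosis of sarcoma as confirmed by a sarcoma histopathologist", informed consent, and that the patient was "diagnosed at or referred to one of the participating hospitals". It excludes patients who are "too ill to complete questionnaires". Study design and setting places the questionnaires after consent, with "the first at baseline, preferably before start of treatment or within 4 weeks thereafter".

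The strengths-and-limitations list describes entry differently: "Inclusion of patients at diagnosis minimises recall bias for total interval length". No section states a longest permitted time from diagnosis to consent. None mentions delayed entry, left truncation or a landmark.

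**The concern.** The clock for OS starts at diagnosis, but a patient becomes observable only at consent. Anyone who dies in between never enters. For those who do enter, the time from diagnosis to consent is guaranteed survival, yet a plain Cox model from diagnosis counts it as time at risk.

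If patients with long and short total intervals wait equally long between diagnosis and consent, the extra time largely cancels in the comparison. If they do not, the group with the longer gap looks spuriously safer. The Introduction already discusses a waiting-time paradox, in which a long interval shows no association with worse survival. A hazard ratio pulled down by entry timing could be mistaken for that paradox, and one pushed up could be mistaken for harm from delay.

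**Working it through.** **No plan figure to reproduce.** The article gives no event count, hazard ratio or power for OS or PFS. The 265 per country under Sample size calculation concerns HRQoL and does not bear on this point.

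**Inputs from the article.** 25% of patients with a long interval; 24 months of follow-up; 2 × 265 = 530 patients.

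**Assumed inputs, because the article gives none.** 24-month OS of 50%, 70% or 85%; constant hazards; mean diagnosis-to-consent gap of 1 to 3 months, uniformly distributed; 24 months of follow-up counted from entry.

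**Step 1: share of unobservable time.** At 24-month OS of 70%, the hazard is −ln(0.70)/24 = 0.01486 per month. Mean observed time after entry is (1 − 0.70)/0.01486 = 20.2 months.
- Mean gap 1 month: 1/(1 + 20.2) = 4.7% of counted person-time.
- Mean gap 3 months: 3/(3 + 20.2) = 12.9%.

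Over all scenarios simulated, the share was about 4-15%.

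**Step 2: rough effect on the comparison when the true ratio is 1.** The ratio of rates counted from diagnosis is approximately (1 + gap_short/20.2)/(1 + gap_long/20.2).
- Equal gaps: 1.00.
- 3 months (long) against 1 (short): 1.0495/1.1485 = 0.914.
- 1 month (long) against 3 (short): 1.1485/1.0495 = 1.094.

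**Step 3: Cox models.** In simulations of 400,000 patients per scenario, those dying before consent were removed. A Cox model counting all time from diagnosis was compared with one in which patients enter the risk set at consent. Results at 24-month OS of 70%:

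| True HR | Mean gap long / short (months) | HR from diagnosis | HR, delayed entry | Ratio |
|---|---|---|---|---|
| 1.0 | 1 / 1 | 0.989 | 0.989 | 1.00 |
| 1.0 | 2 / 1 | 0.943 | 0.990 | 0.95 |
| 1.0 | 3 / 1 | 0.897 | 0.991 | 0.91 |
| 1.0 | 1 / 2 | 1.040 | 0.990 | 1.05 |
| 1.0 | 1 / 3 | 1.092 | 0.989 | 1.10 |
| 1.5 | 1 / 1 | 1.490 | 1.490 | 1.00 |
| 1.5 | 2 / 1 | 1.416 | 1.491 | 0.95 |
| 1.5 | 3 / 1 | 1.341 | 1.486 | 0.90 |
| 1.5 | 1 / 3 | 1.654 | 1.490 | 1.11 |

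The delayed-entry values sit slightly below the truth because all rows share one random seed. A repeat with eight new seeds at a true HR of 1 gave delayed-entry averages of 0.998 to 1.002 and almost the same ratios (0.906 for 3 / 1 and 1.105 for 1 / 3 at 70%). The ratio column is the one to read.

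Across 24-month OS of 50%, 70% and 85%, a 1-month difference in mean gap moves the HR by about 5%. A 2-month difference makes it about 9-11% too low or 10-13% too high, depending on which group waits longer.

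**Step 4: comparison with random error.** With an assumed 0.30 × 530 = 159 deaths, the standard error of the log HR is 1/√(159 × 0.25 × 0.75) = 0.183. The 95% limits are then a factor of exp(1.96 × 0.183) = 1.43 each way.

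**Step 5: PFS.** Progression before consent does not bar enrolment, and Case report forms has recurrence and metastases collected as clinical data. The event named in the PFS definition can thus be observed in the gap, so for PFS as defined the gap is not immortal. Selection remains, because patients who died or became too ill before consent are missed.

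**The case against.** **Level of detail.** Diagnosis is a legitimate origin, and a condensed article may leave risk-set handling to an analysis plan that is not shown. That plan may already provide delayed entry, in which case the sponsor need only confirm it. But the article itself fixes the origin, the model and the entry rules, which together produce left truncation. The point is therefore an improvement to a stated analysis, not a complaint about missing detail.

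**No documented difference in gap.** The total interval ends at histological diagnosis, where the gap to consent begins, so a long first period does not imply a long second one. The abstract and the strengths list place inclusion at diagnosis, which suggests short gaps. This largely stands. Against it, the Introduction names referral organisation and travel time, which differ between the two countries, as possible influences on total interval. The same factors could affect time to consent. That makes a difference plausible, not established.

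**Stronger readings.** A reader might infer that the OS hazard ratio is certainly biased, or biased downwards. The documents support neither: equal gaps leave it unchanged, and reversed gaps reverse the sign. A reader might also infer that PFS contains the same immortal time and needs the same remedy. It does not. Delayed entry there would discard progressions that occurred before consent and can be seen in the records.

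**Absolute rates.** Event rates counted from diagnosis are understated even with equal gaps. The stated aims concern associations, however, so this alone harms no planned estimate.

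**Conclusion.** The point holds for OS as a conditional one. The OS data are left-truncated under the stated definition and entry rules, and a Cox model that ignores this is open to a systematic error. Its size depends on one unknown: the difference in mean diagnosis-to-consent gap between interval groups. It is practically nil with no difference, about 5% for 1 month and about 9-13% for 2 months, in either direction. These figures rest on assumed constant hazards, assumed 24-month OS of 50-85% and assumed gaps. The shift is well inside the random error of a study this size, but a larger sample would not remove it. This is a worthwhile low-cost improvement, not a flaw that threatens the study.

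**What to change.** **OS.** Keep diagnosis as the time origin, but let each patient enter the risk set at the consent or inclusion date in the unadjusted and adjusted Cox models. If the analysis set also requires a completed baseline questionnaire, because interval length is taken from it, use the later of the two dates.

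**Reporting.** Tabulate the diagnosis-to-consent gap by interval group. That table alone shows whether the correction matters.

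**PFS.** Keep the main analysis from diagnosis without delayed entry. Report the number of progressions before consent by interval group, and add a sensitivity analysis with entry at consent.

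**Cost.** Early risk sets become slightly smaller. The team must check that the planned SPSS V.25.0, or another routine, accepts entry times in a Cox model. It must also confirm that the consent date is recorded: Case report forms lists the date of diagnosis and says the first form is completed on inclusion, but does not list a consent date. No change to design or recruitment is needed.

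**What remains.** Delayed entry corrects for survival up to consent. It does not correct for exclusion of living patients too ill for questionnaires, which should be stated as a limitation.

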### Missing data

Online questionnaire completion does not allow for missing data, unless participants have not completed the entire questionnaire, as patients are unable to proceed to the next question until all questions on the current page have been answered. Items missing from paper questionnaires will be dealt with as missing at random. The EORTC QLQ-C30 allows imputation of missing values according to the EORTC scoring manual guideline.^43^ Numbers of missing items will be reported.

### Impact of COVID-19 pandemic on QUEST

A national lockdown was introduced across The Netherlands on 16 March and the UK on 23 March 2020, as part of the national strategies to flatten the curve of the COVID-19 pandemic. On 23 March, recruitment for QUEST was finished in The Netherlands, while the recruitment target was almost reached in the UK. The COVID-19 pandemic forced us to put the recruitment on hold in the UK. The negative consequences of the pandemic on cancer diagnostic timelines (prolonged), incidence (reduced) and eventually cancer outcomes have been shown and modelled by several studies.^44–46^ We will therefore discuss the necessity to reopen recruitment in the UK with our statistical department, as patients recruited during the pandemic will not be representative for the sarcoma population outside COVID-19 times and will bias our results.

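### The pandemic section deals with recruitment only, yet a large share of enrolled patients' follow-up questionnaires falls after lockdown, so the planned two-year HRQoL change mixes time since diagnosis with the pandemic period

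*Protocol article*

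**What the plan says.** The section on the impact of COVID-19 gives the dates: "A national lockdown was introduced across The Netherlands on 16 March and the UK on 23 March 2020". It describes recruitment at that point: "On 23 March, recruitment for QUEST was finished in The Netherlands, while the recruitment target was almost reached in the UK". It adds: "The COVID-19 pandemic forced us to put the recruitment on hold in the UK". It cites pandemic effects on diagnostic timelines, incidence and outcomes, and argues that people recruited during the pandemic would not represent the usual sarcoma population. The one action that follows is "We will therefore discuss the necessity to reopen recruitment in the UK with our statistical department". Follow-up forms from patients already in the cohort are not mentioned.

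Table 1 schedules the QLQ-C30, EQ-5D-5L and HADS at baseline and at 3, 6, 12 and 24 months. The Statistical analysis section plans repeated-measures mixed models for "Change in HRQoL during the follow-up period of 2 years and factors associated with changes in HRQoL". The short- and long-interval groups are then compared with adjustment for patient and tumour characteristics and the baseline score. QALYs and distress are handled in the same way. No calendar-period term is named.

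Under Endpoints, the primary endpoint is baseline global health status, and analyses by geographical area are foreseen if numbers allow. The Sample size calculation sets 265 patients per country so that the countries can be compared.

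**The concern.** The pandemic can enter this study by two routes: through who is recruited after March 2020, and through what enrolled patients report after March 2020. The article recognises the first and is silent on the second, although the second concerns data that will be collected whatever is decided about UK recruitment.

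If lockdown shifted HRQoL, utilities or distress, a model with time since diagnosis but no calendar period would attribute that shift to the disease course. Because the UK started later, its patients have more of their early and middle follow-up in the pandemic. A UK-Netherlands difference in follow-up outcomes could then be read as a healthcare-system effect.

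**Working it through.** The article states no post-lockdown share, so there is no figure to reproduce. The shares below are derived from its dates.

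**Inputs**
- Start (S), from Study design and setting: "The study started recruitment at the first centre in the Netherlands in February 2018 and in the UK in October 2018". No day is given, so the first and last day of each month are used.
- Lockdown (L), from the pandemic section: 16 March 2020 (Netherlands) and 23 March 2020 (UK).
- End of accrual (E): UK, 23 March 2020. The Dutch date is not given beyond recruitment being finished by 23 March 2020. Two cases are taken: the planned 18 months (ending August 2019), and accrual up to lockdown.
- Follow-up waves f = 3, 6, 12 and 24 months.

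**Assumptions.** Accrual is uniform, follow-up is counted from enrolment, and death and non-response are ignored.

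**Formula.** A form is due after lockdown if the patient enrolled after L − f, so

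share(f) = [E − max(S, min(E, L − f))] / (E − S).

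When E = L this reduces to min(1, f / (L − S)).

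**UK.** L − S is 17.7 months (from 1 October 2018) or 16.7 months (from 31 October). At 12 months: 12/17.7 = 68% and 12/16.7 = 72%.

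**Netherlands, accrual to lockdown.** L − S is 25.5 or 24.6 months. At 12 months: 12/25.5 = 47% and 12/24.6 = 49%.

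**Netherlands, 18 months' accrual.** The point L − 12 lies 13.5 or 12.6 months after the start, giving (18 − 13.5)/18 = 25% and (18 − 12.6)/18 = 30%. Recruitment ended before L − 3 and L − 6, so those shares are 0%.

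| Wave | UK | NL, 18 months | NL, to lockdown | UK minus NL (points) |
|---|---|---|---|---|
| 3 months | 17-18% | 0% | 12% | 5 to 18 |
| 6 months | 34-36% | 0% | 24% | 10 to 36 |
| 12 months | 68-72% | 25-30% | 47-49% | 19 to 47 |
| 24 months | 100% | 92-97% | 94-98% | 2 to 8 |
| Mean of four waves | 55-56% | 29-32% | 44-46% | about 9 to 27 |

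**From exposure to bias.** Let the pandemic shift a score by d points; the documents give no value for d.
- Spurious 12-month country difference: 0.19d to 0.47d. For an assumed d = 5 this is about 1 to 2.3 points; for d = 10, about 2 to 4.7 points.
- Spurious baseline-to-24-month change: 0.92d to 1.0d, almost the whole shift.

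**The case against.** The strongest reply is that this is an article without its analysis plan, and a period term or pre-lockdown sensitivity analysis would normally be found in that plan. The listed adjusters are not a closed set. That stands as far as it goes: the absence of a model term is not by itself the finding. What remains is that the article devotes a section to pandemic bias and confines its response to recruitment.

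A reader might infer that country comparisons in general are confounded. The documents do not support that. The article ties the international design chiefly to the length of the total interval. Total interval, baseline HRQoL, stage and tumour size come from patients recruited essentially before lockdown. Country reaches follow-up outcomes only through the general country-comparison aim in the sample size section, the conditional geographical subgroups, and country as a possible factor in the change models. At 24 months the two countries are almost equally exposed, so the problem there is time, not country.

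A reader might also infer that the short-versus-long comparison is biased. A shift common to both groups largely cancels. Bias would need interval length to be related to enrolment date, or a pandemic effect that differs between the groups, and the documents show neither.

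The figures measure exposure, not demonstrated bias. With d up to 10, the spurious 12-month country difference stays below the 10 points that the article calls clinically meaningful. However, the article also takes a small effect size as its standard for the interval cut-off and uses the same guideline to judge change, so a few points are not clearly negligible.

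**Conclusion.** The point holds for the secondary follow-up analyses of HRQoL, utilities and distress. With 92-100% of 24-month forms due after lockdown, the two-year time trend is almost completely aliased with the pandemic period. This needs no imbalance between groups. At 3-12 months, a UK-Netherlands comparison of these outcomes would have unequal exposure, widest at 12 months.

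The exact shares rest on uniform accrual and on the Dutch end date. The direction, with the UK more exposed, holds across the range examined. A Dutch end earlier than 18 months would lower the Dutch shares and widen the gap: 12 months' accrual from 1 February 2018 gives 0% at 12 months and 88% at 24. The size of any bias depends on d, which is unknown. The primary endpoint is not at risk by this route.

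**What to change.** Extend the pandemic section, or the analysis plan, before follow-up results are examined:

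1. As a sensitivity analysis, add to the mixed models for HRQoL, utilities and HADS a time-varying indicator for forms completed on or after 16 March 2020 (Netherlands) or 23 March 2020 (UK), with its interaction with country. The article does not say that completion dates are held; if they are not, use due dates.
2. Repeat the 3-, 6- and 12-month results on pre-lockdown forms only.
3. State that the 24-month time trend cannot be separated from the pandemic, and report the Dutch recruitment end date.

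Staggered enrolment leaves both pre- and post-lockdown forms at 12 months in each country under both Dutch accrual cases, so the indicator can be estimated there. If Dutch accrual took 18 months, its 3- and 6-month forms are all pre-lockdown, and the indicator at those waves rests on UK data.

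The cost is one derived variable, a few sentences and slightly wider intervals for time and country effects. The limits should be stated. A single indicator treats all post-lockdown forms alike and is nearly collinear with the 24-month visit. The pre-lockdown subset keeps only earlier enrolees, about 28-32% of UK 12-month forms (100% minus 68-72%).
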